### 3.2. Gut microbiota

A *t*-test and Wilcoxon analysis will be used to identify the different microorganisms. A principal component analysis (PCA), a principal coordinate analysis, a non-metric multidimensional scaling, and a unweighted pair-group method with arithmetic means will be used to analyze beta diversity. An alpha diversity analysis will be performed using violin plots consisting of the chao1 index, the Shannon index, and the Simpson index. The COG family information and functional prediction of intestinal microbiota will be performed on Phylogenetic Investigation of Communities by Reconstruction of Unobserved States (PICRUSt2).

### 3.3. Serum metabolomics

#### 3.3.1. Metabolomic data preprocessing

Raw data are acquired using UNIFI 1.8.1, and the resulting mass spectra will be exported into Progenesis QI version 2.3 (Non-linear Dynamics, Newcastle, UK) for further analysis, including baseline filtering, peak identification, integral, retention time correction, peak alignment, and normalization, with the main parameters as follows: 5 ppm precursor tolerance, 10 ppm product tolerance, and 5% production threshold. Qualitative analysis will be performed *via* the Human Metabolome Database (HMDB), Lipidmaps (version 2.3), Metlin, the Electron Microscopy Data Bank, Protein Model Data Base, and self-built databases.

The extracted data will be removed if there are any peaks with a missing value of more than 50% or if the compounds with the resulting scores are below 36 (out of 60) points. A data matrix will be formed and imported into R. PCA will be carried out to observe the overall distribution among the samples and the stability of the whole analysis process.

#### 3.3.2. Differential expression analysis of metabolomics data

Orthogonal partial least squares discriminant analysis (OPLS-DA) and partial least squares discriminant analysis (PLS-DA) will be applied to seek differential metabolites between the healthy control and experimental group. Variable importance in projection (VIP) in the OPLS-DA model will be applied to investigate differentially expressed metabolites with biological significance. We will further perform a two-sided Student's *t*-test to verify whether the metabolite differences between the two groups are significant. If a metabolite has VIP values >1.0 and a *P*-value of <0.05, it will be selected as a differential metabolite. Functional pathway and network analysis *via* KEGG (https://www.kegg.jp/) database will be used to explore potential therapeutic targets of QHN therapy in children with tic disorders.

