Most studies regarding the mechanism of acupuncture therapy for tic disorders are conducted *via* animal model experiments, which focus on acupuncture regulating neurotransmitters (32, 33). Studies investigating the mechanism in the clinical context are insufficient. Recently, omics analyses have been used as prospective methods to probe acupuncture mechanisms in the clinical context. Using gut microbiome sequencing, acupuncture was found to modulate the structures and diversity of the gut microbiome, inhibit inflammation of the central nervous system (34, 35), gradually improve gut barrier function, and regulate neurotransmitters (36, 37) in various neuropsychiatric diseases. As for metabolomics assays, the potential mechanisms of acupuncture to treat neuropsychiatric disorders may be associated with modulating systematic inflammation and improving lipid metabolism (38–40). QHN therapy shows effectiveness in the treatment of tic disorders in clinical practice and is worth investigating to determine the specific mechanism. Nevertheless, omics studies of tic disorders are in their infancy (25, 41), with few studies on acupuncture. We aimed to determine how QHN therapy works in the treatment of tic disorders by investigating how it influences the gut microbiota and serum metabolites in children with tic disorders and to analyze possible correlations between clinical profiles and the changes in the gut flora and serum metabolites.

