**Figure 4 F4:**
[figure not shown]
Location of acupoints.

We aim to apply QH needles (patent no. ZL2015 20271867.0; 0.3 × 0.13 × 30 mm; QH; Chongqing Figure 3) in the acupuncture treatment. Manipulation (48) will be done as follows. After skin disinfection, the QH needles will be inserted vertically into the myofascial. Then, the needle will be directed toward the diseased site, and its handle will be gently moved from side to side at an angle of 15–30. When the “de qi” sensation (feelings of numbness, tingling, swelling, soreness, or muscle weakness) becomes obvious (~10 s after stimulation), the needle will be withdrawn. The pinholes will be pressed with a sterile, dry cotton ball without needle retention. As for the Baihui acupoint, the needle will be inserted perpendicularly into the galea aponeurotica, then withdrawn slightly, and the abovementioned manipulation will be performed. As for the Yintang acupoint, the needle will be inserted obliquely into the subcutaneous, and the abovementioned manipulation will be performed.

Participants in the experimental group will receive eight sessions of acupuncture treatment (two times a week for 4 weeks), and participants in the healthy control group will not receive the intervention.

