### 2.5. Outcome evaluations

The clinical evaluations include the assessment of the severity of tics and gastrointestinal symptoms. The recurrence rate will be measured after a 12-week follow-up. The primary outcome measure will be the Yale Global Tic Severity Scale (YGTSS), and secondary outcomes will consist of the gastrointestinal severity index (GSI) and the recurrence rate. Biological specimen analysis outcomes will include changes in the composition of intestinal microbiota, serum metabolites, and serum zonulin. YGTSS and GSI will be assessed at baseline and after 4 weeks when the interventions have been completed. Data relating to the recurrence rate will be collected after a 12-week follow-up. Feces and serum samples will be collected at baseline and 4 weeks after the interventions. If sample collection is concurrent with a treatment, sample collection will be performed after all interventions have been completed. The feces sample will be collected as soon as possible after completing all interventions.

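### For serum metabolites, section 3.3.2 states only a healthy-control versus patient contrast with no time point, which does not test the change under Qihuang needling that the trial sets as its aim, yet its output feeds the therapeutic-target exploration

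*Protocol article*

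**What the plan says.** The aim at the end of the Introduction is to learn how the therapy works by "investigating how it influences the gut microbiota and serum metabolites in children with tic disorders". Section 2.5 lists the specimen outcomes as changes, serum metabolites among them, and schedules the samples: "Feces and serum samples will be collected at baseline and 4 weeks after the interventions". Section 2.4.1 makes the comparison group untreated: "participants in the healthy control group will not receive the intervention".

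Section 3.3.2 gives the metabolite analysis. OPLS-DA and PLS-DA "will be applied to seek differential metabolites between the healthy control and experimental group", followed by a "two-sided Student's *t*-test to verify whether the metabolite differences between the two groups are significant". The selection rule is: "If a metabolite has VIP values >1.0 and a *P*-value of <0.05, it will be selected as a differential metabolite". KEGG pathway and network analysis then "will be used to explore potential therapeutic targets of QHN therapy in children with tic disorders". No time point is given for any of these steps, and no before-after comparison of metabolites is stated.

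Section 3.1.1 treats zonulin, also measured in serum, differently. It plans a paired before-after test in the experimental group for YGTSS, GSI and zonulin, and separately a matched-group comparison of zonulin that is explicitly at baseline.

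**The concern.** The quantity that answers the aim is the within-child change in each metabolite from baseline to the end of treatment. The stated contrast is a different quantity: a difference between children with tic disorders and healthy children. Depending on the samples used, it shows what the disease looks like, or what disease and treatment look like together.

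The use made of the result raises the stakes. The metabolites that pass the rule are the ones that section 3.3.2 goes on to interpret as potential targets of the therapy. If the list comes from a control-versus-patient contrast, it can contain metabolites that needling does not touch and leave out those it corrects. The metabolomic part of the mechanistic question would then be answered from the wrong comparison, although the right samples had been collected.

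**Working it through.** **The plan's own figure.** Section 2.3 starts from 15 per group and allows 20% dropout: 15 / (1 − 0.20) = 18.75, so 19 per group and 38 in total. The article plans 20 and 40, and 20 × 0.80 = 16, which meets the minimum of 15. The figure is reproduced to within rounding and does not bear on this point. No effect size or power lies behind the 15.

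**What each contrast estimates.** For one metabolite, let D be the disease difference at baseline (patients minus controls) and T the mean change in patients over the treatment period. Take the controls as stable.

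- Controls versus patients at baseline estimates D.
- Controls versus patients after treatment estimates D + T.
- Patients after minus before estimates T.

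Only the third isolates T. Leaving the time point open does not help, because neither choice gives T.

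**Illustration.** Inputs from the document: 15 to 20 children per group (section 2.3), and an unpaired two-sided t-test at P < 0.05 (section 3.3.2). Assumptions that are not in the document: SD 1, effects of 1 SD, and within-child correlation r of 0.3 to 0.7.

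Noncentrality of the unpaired test is d × √(n/2):
- n = 15: 1 × √7.5 = 2.74 on 28 df, power about 75%.
- n = 20: 1 × √10 = 3.16 on 38 df, power about 87%.

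Noncentrality of the paired test is T × √(n / (2(1 − r))):
- n = 15, r = 0.3: √(15/1.4) = 3.27 on 14 df, power about 86%.
- n = 15, r = 0.7: √(15/0.6) = 5.00 on 14 df, power above 99%.
- n = 20, r = 0.3: √(20/1.4) = 3.78 on 19 df, power about 95%.
- n = 20, r = 0.7: √(20/0.6) = 5.77 on 19 df, power about 100%.

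A simulation with 20,000 runs per setting gives the same values. Chance of P < 0.05:

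| True state | Controls vs baseline | Controls vs post-treatment | Paired, before vs after |
|---|---|---|---|
| D = 1, T = 0 (needling has no effect) | 75–87% | 75–87% | about 5% |
| D = 1, T = −1 (fully normalised) | 75–87% | about 5% | 86–100% |
| D = 0, T = 1 (treatment change only) | about 5% | 75–87% | 86–100% |

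These are rates for the t-test alone. The plan also requires VIP > 1.0, so actual selection by the planned rule can only be less frequent. In the baseline column the first two rows are the same: that comparison cannot separate a metabolite that responds from one that does not. In the post-treatment column the unaffected metabolite is flagged and the normalised one is missed.

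**Other sections.** Section 3.1.1 plans its paired test for YGTSS, GSI and zonulin only. Section 3.4 computes Spearman correlations of ASVs, metabolites and clinical parameters across the same samples. It mentions no change score, so it does not supply a before-after test of metabolites.

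**The case against.** The best defence is that a condensed article leaves detail to the full protocol. The outcome in section 2.5 is already worded as change, section 3.3.2 never says that its contrast is the only one, and the study calls itself exploratory. This stands in part: a paired analysis may well be intended. It does not remove the mismatch. The article itself states the contrast, the test, the selection rule and the use of the output, and these do not fit its aim. For zonulin the same article spells out both a paired test and a baseline group test.

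A second defence is that the control contrast could be run at both time points, so that a normalised metabolite would differ at baseline and not afterwards. That is fair, and the 5% figure applies to the post-treatment comparison alone. Setting one significant result beside one non-significant result is still not a test of change.

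Several stronger readings are tempting, and the document does not support them.

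- A reader might infer that nothing in the trial tests change under needling. Section 3.1.1 does so for YGTSS, GSI and zonulin.
- A reader might infer that the stated contrast holds no information on treatment. That is true only at baseline; after treatment the effect is present but mixed with disease.
- A reader might infer that targets will be declared. The text speaks of exploring potential ones.
- Section 3.3.1 says "The extracted data will be removed if there are any peaks with a missing value of more than 50" percent, and a reader might infer that a metabolite appearing only after treatment would be deleted. That requires missingness pooled over all groups and times, which the section does not state.
- A reader might extend the error to taxa. Section 3.2 names neither groups nor time points for its tests, so it fixes no wrong contrast.

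**Conclusion.** The point holds for serum metabolites. Followed as written, section 3.3.2 selects disease differences, or disease mixed with treatment change, and passes them on as candidates for how the therapy works. It states no test of the change in metabolites that the Introduction and section 2.5 promise. The fault lies in which contrast is stated, so it does not depend on any numerical assumption.

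The size of the consequence does depend on assumptions. With 1 SD effects, 15 to 20 per group and r from 0.3 to 0.7, an unaffected metabolite passes the t-test in about 75% to 87% of trials. A fully normalised one passes in about 5% of trials if controls are compared with post-treatment samples. Smaller effects would lower the first figure without changing what each contrast measures.

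**What to change.** In section 3.3.2:

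1. State a paired baseline-to-4-week comparison within the experimental group as the contrast that feeds the KEGG target exploration, using a paired test on log intensities or a paired (multilevel) OPLS-DA.
2. Label healthy control versus patients at baseline as a separate disease-signature contrast, and analyse it in a way that respects the matching.
3. State the limit of the paired result. With no untreated tic group, and with tics that wax and wane by the article's own account, it shows change under treatment and cannot be attributed to needling alone.

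Movement toward the control level should not become a selection rule; at most it can be described. The gap from controls and the change share the same baseline values, and their correlation is √(1 − r)/2 in size: 0.42 at r = 0.3 and 0.27 at r = 0.7. In a simulation with no disease and no treatment effect, 72% to 84% of falsely significant paired changes moved toward control, where an independent check would give 50%.

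The cost is a few sentences and a little more analysis. No new samples are needed.

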## 2. Methods and analysis

### 2.1. Study design and participants

This is a matched-pairs design, controlled, clinical trial with two groups (experimental group and healthy control group). Patients with tic disorders and age–gender-matched healthy children will be recruited through advertisements posted on web pages and display boards or through the outpatient system recommended by doctors at Panyu Hospital of Chinese Medicine (Guangzhou, China) and Foshan Fosun Chancheng Hospital (Foshan, China). Both hospitals are tertiary hospitals. All participants will be screened according to the inclusion and exclusion criteria. The guardians of eligible participants will sign a written informed consent (see Supplementary material 1) after a detailed explanation of the study by the investigators and will be provided with a baseline assessment. Participants are free to withdraw from the study at any time. This protocol was designed according to the Standard Protocol Items: Recommendations for Interventional Trials (SPIRIT) guidelines (42) and the Standard Protocol Items for Clinical Trials with Traditional Chinese Medicine 2018: Recommendations, Explanation, and Elaboration (SPIRIT-TCM Extension 2018) (43). The study was registered in the Chinese Clinical Trial Registry (ChiCTR2200057723).

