Withdrawal criteria and management	1. Misdiagnosis, violation of the inclusion criteria	
	2. Self-use of prohibited treatment	
	3. Poor cooperation with the established treatment or data collection procedures	
	4. Serious adverse events or life-threatening diseases or an acute progression of the disease occurs during the trial	
	5. Obvious discomforts arise because of the therapy	
	6. Participants request withdrawal voluntarily	

American Psychiatric Association (1).

* Healthy control matching procedure: To select a healthy control group comparable in size to the experimental group. The criteria used for this procedure (with match tolerance) are as follows: (1) age (±1 year), (2) sex (exact match), (3) family history of the psychiatric condition (exact match), (4) parental marital status (exact match), (5) mode of delivery (exact match), and (6) birth weight (±100 g). We chose to match these variables as they may be the risk factors influencing the development of tic disorders.

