### 3.1. Statistical analysis

#### 3.1.1. Clinical data and serum zonulin

For the clinical data, statistical analyses will be performed using SPSS Statistics 24.0 (IBM SPSS Statistics, Armonk, NY). Children in the experimental group will be matched to their peers in the healthy control group on age, sex, family history of a psychiatric condition, parental marital status, mode of delivery, and birth weight. Categorical variables will be described in the form of frequencies or percentages. Continuous variables will be presented as mean ± standard deviation or median and range. The chi-square test or Fisher's exact test will be used to compare the change in the categorical variables. Changes in YGTSS, GSI, and concentration of serum zonulin in the experimental group before and after treatment will be analyzed using paired sample *t*-test if the data conform to a normal distribution. The Wilcoxon paired-samples signed-rank test will be performed if the data do not conform to normal distribution or if there are differences in variance uniformity. Differences in concentration of serum zonulin between two matched groups at baseline will be analyzed with the above statistical methods. The results are based on two-sided tests, and a *P*-value of <0.05 will be considered statistically significant.

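### The metabolite comparison between individually matched groups is written as an ordinary Student's t-test, and an equal-variance rule that a paired test does not need can switch the primary test

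*Protocol article*

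**What the plan says.** Section 2.1 of the Protocol article sets the design: "This is a matched-pairs design, controlled, clinical trial with two groups". The footnote to Table 1 (section 2.2) gives a tolerance for each of six matching variables. Age is matched within 1 year and birth weight within 100 g; sex, family history, parental marital status and mode of delivery are matched exactly. The analysis section repeats this: "Children in the experimental group will be matched to their peers in the healthy control group on age, sex, family history of a psychiatric condition", followed by the other three variables.

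Section 3.1.1 gives paired tests to the before-after changes in YGTSS, GSI and zonulin. It applies the same methods to zonulin between the two matched groups at baseline. The signed-rank test replaces the paired t-test "if the data do not conform to normal distribution or if there are differences in variance uniformity". For categorical data it says: "The chi-square test or Fisher's exact test will be used to compare the change in the categorical variables".

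For metabolites, section 3.3.2 names a "two-sided Student's *t*-test to verify whether the metabolite differences between the two groups are significant" and makes its result a selection rule: "If a metabolite has VIP values >1.0 and a *P*-value of <0.05, it will be selected as a differential metabolite". Pairing is not mentioned there.

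**The concern.** The same matched children are treated as pairs for one serum marker and, on the natural reading, as two independent samples for all other serum metabolites. An independent-samples test uses a standard error that ignores any correlation the matching has created. If that correlation is positive, the standard error is too large, P-values are too large, and fewer true differences pass the 0.05 gate. That gate decides which metabolites are called differential, and the pathway analysis of possible therapeutic targets follows it. With 15 to 20 pairs there is little power to spare.

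The variance rule is a separate fault. A paired t-test uses only the within-pair (or within-child) differences, so unequal spread before and after treatment has no bearing on its validity. Yet the rule governs YGTSS, the primary outcome. Treatment to which some children respond and others do not can itself change the spread between baseline and week 4, so the rule could fire for a reason unrelated to whether the t-test is sound.

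The sentence on categorical variables speaks of change. Chi-square and Fisher's exact test assume independent observations, so they would not fit any category compared before and after in the same children.

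**Working it through.** **Inputs from the protocol.** At least 15 per group, 20% dropout, 20 per group recruited (section 2.3). Two-sided 0.05 (sections 3.1.1 and 3.3.2). Six-variable individual matching (section 2.2).

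**Assumptions.** The protocol gives no within-pair correlation ρ, SD or effect size. I take ρ from 0 to 0.7, a standardised shift d of 0.6 and normal data.

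**The plan's own figure.** 15 / (1 − 0.20) = 18.75, so 19 per group. The stated 20 per group (40 in total) agrees with this, with slight rounding up. The protocol states no power, so there is none to reproduce.

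**Metabolite test.** In SD units, the true standard error of the mean difference over n pairs is √(2(1 − ρ)/n). The independent-samples test uses about √(2/n). The ratio of the first to the second is √(1 − ρ): 0.949, 0.837, 0.707 and 0.548 at ρ = 0.1, 0.3, 0.5 and 0.7.

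The paired test's noncentrality is d√n / √(2(1 − ρ)). With d = 0.6 and n = 20 the numerator is 0.6 × 4.472 = 2.683. The critical value is 2.093 on 19 df, against 2.024 on 38 df for the unpaired test. Paired power is from the noncentral t distribution; the unpaired figures are from 200,000 simulated trials per cell.

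| Assumed ρ | Paired noncentrality | Unpaired power | Paired power | Unpaired type I error |
|---|---|---|---|---|
| 0 | 2.683/1.414 = 1.897 | 46% | 44% | 5.0% |
| 0.1 | 2.683/1.342 = 2.000 | 45% | 48% | 4.0% |
| 0.3 | 2.683/1.183 = 2.268 | 45% | 58% | 2.0% |
| 0.5 | 2.683/1.000 = 2.683 | 44% | 72% | 0.7–0.8% |
| 0.7 | 2.683/0.775 = 3.464 | 43% | 91% | 0.1% |

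The paired test holds 5% throughout. At the protocol's minimum of 15 pairs and an assumed shift of 0.8 SD the pattern is the same: unpaired versus paired power is 56% versus 53% at ρ = 0, 57% versus 68% at 0.3 and 59% versus 82% at 0.5. Only a negative correlation would make the unpaired test liberal (7.2% at ρ = −0.2, n = 15).

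**Variance trigger.** The paired t-test was simulated with no true difference, ρ = 0.5, and marginal SD ratios of 1, 2 and 3. With 15 or 20 pairs its type I error stayed between 4.9% and 5.1%. Unequal variances do no harm, so the trigger protects against nothing.

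**Categorical variables.** Section 3.1.1 does not say which variables are meant, and no before-after categorical outcome is named elsewhere. I therefore attach no power figure to this part.

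**The case against.** Section 3.3.2 never says unpaired or independent, so a paired test may have been intended. That is possible. But section 3.1.1 says paired when it means paired, and the text needs correcting on either reading.

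Nothing in the protocol supports a correlation of 0.5 to 0.7. The pairs are unrelated children, matched on variables chosen as possible risk factors for tic disorders, not as predictors of metabolite levels. At 0 to 0.1 the two tests differ by 2 to 3 points, and at 0 the unpaired test is slightly ahead. This stands, which is why the size is given as a range starting at zero.

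The t-test is one gate beside the VIP threshold, in work that section 2.3 calls exploratory. This also stands and limits the consequence.

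Several stronger readings are tempting and fail:
- That the matching is wasted throughout: YGTSS, GSI and both zonulin comparisons already have paired tests.
- That the P-values generate false findings: under positive correlation they err on the cautious side.
- That the t-test is run on raw intensities: section 3.3.1 includes normalization and simply does not mention a log transform.
- That YGTSS severity class is compared before and after: section 2.5.1.1 gives the bands only to describe the scale, and section 3.1.1 tests YGTSS as a continuous change. Recurrence is collected once, after follow-up.
- That section 3.2 fixes unpaired tests for taxa: it is silent on pairing, which in a condensed article is not an error.

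**Conclusion.** The point holds for two stated rules. First, the metabolite gate is worded as an independent-samples test although the design is individually matched and zonulin in the same groups is paired. The loss depends on an undocumented correlation: none at 0, about 13 points of power at 0.3 (58 − 45) and about 28 at 0.5 (72 − 44), for 20 pairs and a shift of 0.6 SD. Second, the equal-variance trigger has no role in choosing between two paired tests. A reader might infer that it invalidates the primary P-value. It does not, because the signed-rank test is itself a paired test; the fault is an unnecessary data-driven choice of the primary analysis. The chi-square and Fisher sentence needs only a conditional clarification. The changes are worth making because they cost almost nothing; the primary analysis is not invalid as it stands.

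**What to change.** - **Section 3.3.2:** name a paired t-test or signed-rank test on within-pair differences for comparisons of patients with their matched controls. Alternatively, use a model with a pair effect, which keeps the remaining member of a pair broken by dropout. Say which is used.
- **Section 3.1.1, continuous outcomes:** delete the variance-uniformity condition and state that normality is judged on the paired differences.
- **Section 3.1.1, categorical variables:** limit chi-square and Fisher's exact test to independent groups. For any category compared before and after in the same children, use McNemar's test, or a marginal homogeneity test for ordered classes.

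These are wording changes; no extra data are needed. The paired test has fewer degrees of freedom (19 rather than 38 with 20 pairs). If the pair correlation is zero, that costs about 2 points of power at 20 pairs (46% to 44%, d = 0.6) and about 3 at 15 pairs (56% to 53%, d = 0.8).

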##### 2.5.3.2. Serum metabolomics

The blood sample will be collected using a butterfly needle and syringe. In total, 3 ml of blood will be drawn into a serum tube and centrifuged, and 1 ml of aliquots will be transferred into three tubes and stored in a freezer at −80°C for the analysis of metabolomics. Metabolic profiling in both electrospray ionization (ESI) positive and ESI negative ion modes will be analyzed using the AB ExionLC System (ABSCIEX, Framingham, MA) coupled with a Q-Exactive quadrupole-Orbitrap mass spectrometer with a heat ESI source (Thermo Fisher Scientific, Waltham, MA). An ACQUITY UPLC HSS T3 column (100 × 2.1 mm, 1.8 μm) will be used in the positive and negative modes. The binary gradient elution system consists of (A) water (containing 0.1% formic acid, v/v) and (B) acetonitrile (containing 0.1% formic acid, v/v). The flow rate is 0.35 ml/min, and the column temperature is 45°C. A non-targeted metabolite analysis will be performed by Luming Biological Technology Co. Ltd. (Shanghai, China).

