### 3.4. Correlation analysis of the microbiome and metabolome

Spearman's rank correlation coefficient will be calculated for all ASV-metabolite pairs and clinical parameters using the data across the same samples. A network analysis is to be performed on the interaction matrix using the fast greedy community algorithm in the igraph R package. This algorithm identifies subgraphs using direct optimization of a modularity score. Each discovered community is annotated according to the KEGG pathways of the metabolites within the community.

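### Differential metabolites are chosen by VIP>1 and an unadjusted P<0.05; the VIP condition adds almost no protection, so a sizeable share of the list may be false

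*Protocol article*

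**What the plan says.** The serum assay is untargeted (protocol article, section 2.5.3.2): "A non-targeted metabolite analysis will be performed by Luming Biological Technology Co. Ltd". The number of features expected is not stated.

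Section 3.3.2 compares the healthy controls with the experimental group in three steps. First, the discriminant model: "Variable importance in projection (VIP) in the OPLS-DA model will be applied to investigate differentially expressed metabolites with biological significance". Second, a univariate test: "We will further perform a two-sided Student's *t*-test to verify whether the metabolite differences between the two groups are significant". Third, the decision: "If a metabolite has VIP values >1.0 and a *P*-value of <0.05, it will be selected as a differential metabolite". The section then turns to KEGG pathway and network analysis to look for potential therapeutic targets of the needle therapy.

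The article mentions no q-value, Bonferroni correction or permutation step. Section 3.3.1 lists the preprocessing steps but not how the variables are scaled before OPLS-DA. Section 2.3 sets at least 15 children per group, plans 20, and calls the research exploratory.

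**The concern.** The metabolite rule is complete as written: a feature that meets both conditions is differential. It is therefore a stated choice, not a detail left to a fuller plan, and a later plan that applied false-discovery control would contradict it.

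The rule looks like a double safeguard, with the t-test presented as verifying what VIP found. But both quantities measure how strongly a metabolite separates the same two groups of children. If VIP>1 is met by nearly everything with P<0.05, the rule reduces to an unadjusted 5% test repeated over every feature.

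At stake is the list from which potential therapeutic targets are to be sought. The Discussion (section 5) expects multi-omics analysis to elucidate such targets, so readers need to know how much of the list chance alone could supply.

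**Working it through.** **Inputs from the article.** VIP>1.0 and two-sided P<0.05 (3.3.2); at least 15 per group, 20 planned, 20% dropout (2.3).

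**Assumed, because not given.** 1000 metabolites; 5%, 10% or 20% truly different; standardised difference d=0.8 (d=1.2 as a variant); unit-variance or Pareto scaling.

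**The plan's own figure.** 15/(1-0.20) = 18.75, so 19 per group; the planned 20 leaves 20 x 0.8 = 16, which is at least 15. The sample size is consistent. The article gives no omics error rate to reproduce.

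**Step 1: what VIP>1 requires.** With one predictive component and unit-variance data, VIP² for a metabolite equals its r² with group divided by the mean r² over all metabolites. Mean VIP² is therefore 1, and VIP>1 means only above average. With no true differences, mean r² is about 1/(N-1), where N is the total number of children. P<0.05 requires r² > t²/(t²+N-2), with t the two-sided 5% critical value.

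| Per group | N | r² needed for VIP>1 (null) | r² needed for P<0.05 |
|---|---|---|---|
| 15 | 30 | 1/29 = 0.034 | 0.130 |
| 20 | 40 | 1/39 = 0.026 | 0.097 |

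On the t scale the null VIP threshold is t² = 28 x (1/29)/(28/29) = 1 at n=15, that is |t|>1. About 32-33% of pure-noise features pass it, and every feature with P<0.05 already has.

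**Step 2: simulation check.** With 1000 features, independent or block-correlated, and unit-variance scaling, adding VIP>1 removed none of the roughly 50 false selections. With Pareto scaling it removed about 3% of them under the null and up to about 20% when many features truly differed. It also removed true features, so the false share hardly moved (for example 44.3% to 43.5%; the largest fall was about 3 percentage points).

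**Step 3: false selections if nothing differs.** Expected number = 0.05 x m, where m is the number of metabolites: m=200 gives 10, 500 gives 25, 1000 gives 50, 5000 gives 250.

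**Step 4: false share when some metabolites differ.** In the simulations about 56% of true features at d=0.8 were detected at n=15 and about 69% at n=20. For m=1000:

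- 5% true, n=15: false 950 x 0.05 = 47.5; true 50 x 0.56 = 28; false share 47.5/75.5 = 63%.
- 10% true, n=15: false 900 x 0.05 = 45; true 100 x 0.56 = 56; false share 45/101 = 45%.
- 20% true, n=15: false 800 x 0.05 = 40; true 200 x 0.56 = 112; false share 40/152 = 26%.
- 10% true, n=20: false 45; true 100 x 0.69 = 69; false share 45/114 = 39%.

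Over both sample sizes and both scalings, the simulated shares were 56-63% with 5% true, 37-45% with 10% and 20-26% with 20%. With 10% true at d=1.2 they were 29-34%.

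**Step 5: effect of matching.** Controls are matched on six variables (Table 1 footnote), and the t-test is not described as paired. With within-pair correlation rho, the unpaired test's null rate is about P(|Z| > 1.96/sqrt(1-rho)). An assumed rho of 0.1 gives 3.9%, and 0.3 gives 1.9%. The 50 per 1000 would become about 39 or 19.

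**Step 6: Benjamini-Hochberg at 5%, 10% true, d=0.8.**

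| Per group | Current rule: selected (false) | Benjamini-Hochberg: selected (false) |
|---|---|---|
| 15 | about 101 (45) | about 5 (0.3) |
| 20 | about 113 (45) | about 17 (0.7) |

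With no true differences, false selections fall from about 48-52 to 0.04-0.11 per study.

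**The case against.** The strongest reply is that this is exploratory work, labelled so in section 2.3. Section 3.3.2 speaks only of exploring potential targets, and the clinical outcomes do not depend on this list. A strict filter at 15 per group would also discard most real signals: the current rule finds about 56 of 100 true features, while Benjamini-Hochberg at 5% selects about 5 features in all, possibly too few for pathway analysis. These points stand. They lower the severity and shape the remedy, but they do not make an unadjusted list interpretable.

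Two technical replies also stand in part. That VIP removes nothing is exact only for one predictive component and unit-variance scaling; since the scaling is not stated, the fair wording is almost no protection. And 50 per 1000 is nearer an upper figure if matching induces positive within-pair correlation. Nor do false selections outnumber true ones in general: among the scenarios examined, this happens only with 5% true at d=0.8 or with no signal.

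A reader might infer that taxa and microbe-metabolite correlations are also declared at raw P<0.05. The article does not say so. Section 3.2 names tests ("A *t*-test and Wilcoxon analysis will be used to identify the different microorganisms") without a threshold, and section 3.4 says only this: "Spearman's rank correlation coefficient will be calculated for all ASV-metabolite pairs and clinical parameters using the data across the same samples". The general 5% level sits in section 3.1.1, under clinical data and serum zonulin. Silence on thresholds there is detail a condensed article may leave to a fuller plan, and without a stated cut-off no count of chance correlations can be given. A reader might also suppose that the selected metabolites feed the community network; section 3.4 builds that network from all pairs.

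**Conclusion.** The concern holds for the metabolite rule in section 3.3.2 and is limited to it. An untargeted screen is judged at an unadjusted 5% level, and the VIP condition is nearly redundant with the t-test.

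The sizes in the working rest on an assumed 1000 metabolites, 15 to 20 children per group, the assumed signal levels, and an unpaired test with no within-pair correlation. The expected number of chance selections scales with the number of metabolites. The false share depends instead on the proportion truly different and on the effect size; over the levels tried it ran from about one fifth to nearly two thirds, and it is 100% if nothing differs.

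This should be fixed, but it does not threaten the trial's primary result.

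**What to change.** In section 3.3.2:

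- Define a differential metabolite by a Benjamini-Hochberg q-value across all metabolites tested: q<0.05, or q<0.10 labelled exploratory.
- Use VIP only to rank metabolites, and state the scaling.
- Interpret the OPLS-DA model only if its cross-validated Q2 exceeds that from permuted group labels.
- Base any statement about therapeutic targets on metabolites that survive false-discovery control.
- A raw-P list may still be shown, or used for pathway screening, if it is labelled hypothesis-generating and carries q-values alongside.

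The cost is one paragraph of wording and a short permutation run, with no new data and no change for participants. The real price is the shorter list shown in the working; keeping the labelled raw-P list softens it. The change should be made before the omics data are analysed, since choosing the error control after seeing the lists would itself introduce bias.
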